#### Smoking cessation treatments chosen

The proportion of LSSS clients choosing each available treatment option will be calculated from the information provided in the routine stop smoking service.

#### Patient experiences

We have developed a patient satisfaction questionnaire, which will be used to collect information on the experiences of service users. This will be examined for the intervention group using appropriate multilevel models.

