#### Study questions

Primary study questions:

1. What are the rates at which the population of Pakistani and Bangladeshi male smokers will set a quit date with the stop smoking services in the intervention and control areas?

2. What proportions of those setting a quit date in the intervention and control areas achieve biochemically verified prolonged abstinence from smoking at a) 4 weeks, b) 3 months and c) 6 months after the agreed quit date?

3. What is the likely degree of contamination of the intervention and control areas and the design effects that need to be taken into consideration when conducting sample size calculations for a definitive cluster randomised controlled trial?

4. What are the key components of the intervention as it develops and how do these components relate to the outcome measured by the rates of setting quit dates and abstinence among those setting quit dates?

Secondary study questions:

5. What proportion of Pakistani and Bangladeshi male smokers that book an appointment with the stop smoking service attend the initial appointment and set a quit date in the intervention and control areas?

6. What smoking cessation treatments do Pakistani and Bangladeshi men use in the intervention areas, facilitated by outreach workers, and in the control areas, without such workers?

7. What are the experiences of the services of the relevant groups in each of the trial arms and how satisfied are they?

8. What proportions of those enrolled adhere to the interventions chosen?

9. What impact, if any, are these interventions likely to have on smokeless (oral) tobacco use in these smokers?

10. What are the costs, from a health service perspective, of delivering these interventions?

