**Extended Dataset**		

6. What smoking cessation treatments do Pakistani and Bangladeshi men use in the intervention areas, facilitated by outreach workers, and in the control areas, without such workers?	Numbers of clients choosing each available treatment option (e.g. NRT, Zyban etc)	LSSS Routine database Patient satisfaction questionnaire administered by LSSS 'Call to Quit' team

7. What are the experiences of the services of the relevant groups in each of the trial arms and how satisfied are they?	Patient satisfaction	Patient satisfaction questionnaire administered by LSSS 'Call 2 Quit' team

8. What proportions of those enrolled adhere to the interventions chosen?	Numbers using oral tobacco during quit attempt (self report) Number of people adhering to each medication used in each arm of the trial (self report) Attendance at clinic in each arm of the trial	Adherence rating week by week then averaged, collected by SSA on extended data monitoring form

9. What impact, if any, are these interventions likely to have on smokeless (oral) tobacco use in these smokers?	Numbers using oral tobacco during quit attempt (self report)	Frequency rating week by week, collected by SSA on extended data monitoring form Frequency of use of oral tobacco during this quit attempt rating on Patient satisfaction questionnaire administered by LSSS 'Call to Quit' team

10. What are the costs, from a health service perspective, of delivering these interventions?	Estimated benefits of the intervention in terms of QALYs or LYGs.	Additional costs to NHS of (i) Employment, training, management of outreach workers- (ii) Extra resources used by LSSS – e.g. medication, behavioural support (Calculated from estimates of extra time used)

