#### Losses to follow-up

Those individuals recruited in the Extended Dataset will be asked about their satisfaction with the stop smoking service they received. It is the experience of LSSS that individuals who return to smoking do not return to clinic, while those who have succeeded do so and are typically very pleased with the care they received. Thus, loss to follow-up is a potentially major bias in assessing these outcomes. However, these individuals will have consented to follow up and thus we seek to minimise loss of information from those who do not stop smoking by telephone contact from the Birmingham Call 2 Quit line.

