#### Estimating adherence

The standard forms for recording the clinical contact with patients record whether the person is using nicotine replacement therapy (NRT) or not, but not degree of adherence, which is quite complicated and impractical for NHS to measure accurately. We will therefore use a measure that defines good or less than good adherence, which is defined for each type of treatment. Stop smoking advisors will be asked to record adherence weekly on a modified routine monitoring form.

This will be modelled with random effects logistic regression, with the numerator being the number of people who adhere well to treatment in each week and the denominator being all those receiving treatment. Repeated measures on the same individuals are correlated within individuals and will be accounted for in the analyses.

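### The satisfaction analysis is specified for the intervention group only, although study question 7 asks about each trial arm; the adherence denominator also needs aligning with question 8

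*Protocol article*

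**What the plan says.** **Satisfaction.** Study question 7, repeated in Table 2, reads: "What are the experiences of the services of the relevant groups in each of the trial arms and how satisfied are they". Table 2 gives the source as a questionnaire administered by the telephone support team and sets no restriction by arm. The Methods paragraph of the Abstract says that the intervention's effect on adherence and on satisfaction will be assessed. Under Extended Dataset, Recruitment, the providers are those who have previously served target men living in intervention or control areas. The analysis, in Patient experiences, is one sentence: "This will be examined for the intervention group using appropriate multilevel models".

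**Adherence.** Study question 8 reads: "What proportions of those enrolled adhere to the interventions chosen". Estimating adherence says: "Stop smoking advisors will be asked to record adherence weekly on a modified routine monitoring form". These ratings go into a logistic model that contains random effects. The section defines the proportion to be modelled in these words: "the numerator being the number of people who adhere well to treatment in each week and the denominator being all those receiving treatment". Under question 8, Table 2 lists self-reported adherence to each medication by arm and, separately, clinic attendance by arm.

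**The concern.** A question about each arm needs a result from each arm, and a statement about the effect of the intervention needs a contrast between them. A model fitted to the intervention group alone supplies neither. Anyone who follows the Patient experiences sentence literally would leave the control questionnaires unanalysed and could not say whether outreach changed satisfaction.

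The adherence issue is smaller. The question and the model name different groups, and the article does not say whether they are meant to be the same men. Under Rationale and Interventions, outreach is expected to work partly by keeping men in treatment. It therefore matters whether men who leave treatment remain in the denominator.

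**Working it through.** The document states no sample size, expected satisfaction score, adherence rate or retention rate for the Extended Dataset, so there is no figure to reproduce. The check is a comparison of text.

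**Satisfaction**
1. Population in the question: both arms (Study questions, question 7; Table 2).
2. Purpose stated: the intervention's effect on satisfaction (Abstract).
3. Data planned: providers serving men from either kind of area (Extended Dataset, Recruitment), and a questionnaire with no arm restriction (Table 2).
4. Analysis specified: the intervention group only (Patient experiences).
5. Items 1 to 3 agree with one another; item 4 contradicts them. The Protocol amendments section does not alter item 4.

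**Adherence**
1. Population in the question: those enrolled.
2. Denominator in the model: "the denominator being all those receiving treatment".
3. The denominator has two possible readings: (a) everyone who started a chosen treatment, or (b) those on treatment in the week in question. The phrase about each week belongs to the numerator, and the text does not settle which reading is meant.
4. Reading (a) is close to question 8. Reading (b) is not.

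To show why the choice should be stated, suppose a proportion *a* of men on treatment adhere well each week, and a proportion *r* of men remain from one week to the next, over *W* weeks. Reading (b) gives *a* whatever the retention. With all starters in the denominator and unattended weeks counted as non-adherent, the figure is *a* × (1 + r + … + r^(W−1)) / W. All inputs below are assumed; none comes from the document. With *a* = 0.80:

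| Weekly retention | Reading (b) | All starters, 4 weeks | All starters, 12 weeks |
|---|---|---|---|
| 100% | 80% | 80% | 80% |
| 95% | 80% | 0.80 × 3.710/4 = 74% | 61% |
| 90% | 80% | 0.80 × 3.439/4 = 69% | 48% |
| 80% | 80% | 0.80 × 2.952/4 = 59% | 31% |

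The table shows only that the definitions diverge when men leave. It does not estimate anything about this trial.

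**The case against.** On satisfaction, the strongest reply is that the sentence is a drafting slip: every other part of the article treats the questionnaire as covering both arms. That is probably so. It lowers the cost of the correction but leaves the stated analysis wrong. A reader might also infer that control men will not be surveyed at all; the recruitment text and Table 2 point the other way.

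On adherence, the reply carries more weight, and three stronger readings should be resisted.

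- *Adherence is rated only on men still in treatment.* The text does not say this. Its denominator can equally mean everyone who received a chosen treatment.
- *The protocol itself says the missing ratings are non-ignorable.* The Extended Dataset section on losses to follow-up does say that "individuals who return to smoking do not return to clinic", but it is discussing satisfaction. Relapse to smoking and poor adherence to medication are different events, and a likelihood-based random effects model can accommodate dropout that depends on earlier recorded adherence. Informative dropout is a reasonable worry, but it is an inference.
- *Question 8 cannot be answered.* Clinic attendance by arm is listed under the same question, so retention is measured separately and does not rest on the adherence rating.

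Assumed inputs can also be chosen so that the two denominators rank the arms in opposite orders. Nothing in the document suggests that such values apply here.

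Finally, scoring every unattended week as non-adherence is debatable. It merges two outcomes that Table 2 keeps apart and misclassifies men who take their medication without attending.

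**Conclusion.** The satisfaction point holds: the specified analysis contradicts study question 7 and the Abstract, and it yields no arm comparison. The adherence point holds only as a mismatch of wording that needs clarifying. Both outcomes are secondary in a pilot, so the primary findings on uptake and abstinence are untouched. The correction should be made, but it does not threaten the trial. The conclusion on satisfaction assumes only that the Patient experiences sentence means what it says. The view that the fix needs no new data assumes that recruitment ran as the Extended Dataset section describes.

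**What to change.** **Patient experiences.** Replace the sentence with one stating that satisfaction will be analysed in both arms, with arm as a covariate and randomised area as a random effect. This follows the multilevel approach already described for the uptake outcome.

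**Estimating adherence.** Define the denominator as all enrolled men who started the chosen treatment, and present the result beside clinic attendance by arm. If unattended weeks are to be counted as non-adherent, do so in a sensitivity analysis, and say which weeks count.

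**Cost.** The satisfaction change is wording only and needs no additional data collection. The main adherence definition is also a wording change. The sensitivity analysis needs a definition of the treatment weeks that count, which this article does not give. The satisfaction comparison may be imprecise, because service use is concentrated in few areas. In the Table 3 baseline, areas 4 to 7 contribute 79 + 155 + 136 + 98 = 468 of the 563 users obtained by summing that column over all 16 areas. It should therefore be reported as an estimate with its interval.

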#### Estimating adherence

The standard forms for recording the clinical contact with patients record whether the person is using nicotine replacement therapy (NRT) or not, but not degree of adherence, which is quite complicated and impractical for NHS to measure accurately. We will therefore use a measure that defines good or less than good adherence, which is defined for each type of treatment. Stop smoking advisors will be asked to record adherence weekly on a modified routine monitoring form.

This will be modelled with random effects logistic regression, with the numerator being the number of people who adhere well to treatment in each week and the denominator being all those receiving treatment. Repeated measures on the same individuals are correlated within individuals and will be accounted for in the analyses.

#### Estimation of costs

We will approach this using the models developed for other purposes (e.g. the National Institute for Health and Clinical Excellence (NICE) reports on NRT[39]). Thus, if long-term abstinence can be estimated, we should be able to use this to derive an estimate of the benefits of the intervention in terms of Quality Adjusted Life Years (QALYs) or Life Years Gained (LYGs). We will therefore estimate the additional costs of:

◦ The employment, training, and management of the outreach workers

◦ The extra resources used, including extra medication, extra behavioural support given by other providers as a result of additional activity generated by the outreach workers. We will calculate this from the economic costs to the NHS estimated from time used and/or observations of extra time taken.

#### Qualitative work

A modified Framework approach will be used systematically to make sense of the different types of qualitative data that will be generated[40]. Issues that emerge from these data will be indexed and collated to form broad categories. The categories will be examined and emergent themes identified in regular discussions of the multi-disciplinary qualitative sub-group, with emerging ideas being incorporated into future rounds of the qualitative data collection.

### Current study status

The intervention period began on 1^st ^November 2007 and ran for 12 months, with an end date of 31^st ^October 2008. Final data collection and analysis of data in relation to the primary outcomes is currently underway and we anticipate will be completed by July 2009.

#### Protocol amendments

From the time of writing this protocol, the following changes have been made.

We aimed to measure the rate at which Pakistani and Bangladeshi male smokers set a quit date with the stop smoking services in the intervention and control areas. We defined reach as the proportion of each relevant ethnic group setting a quit date using the stop smoking service, with the denominator for this being all those of relevant ethnic group attempting to quit during the same period. As this latter number could only be estimated, we investigated whether The Health Survey for England ethnic boosted sample data had the relevant information (i.e. the proportion that tried to stop in the previous year). These data did not, however, contain this information and we have therefore assumed that the proportion of Pakistani and Bangladeshi males that attempt to quit is the same as the proportion of all other ethnic groups. This assumes that what is true of the majority population is true of Pakistani and Bangladeshi populations.

Prior to the start of the study, the randomisation of the intervention and control areas were switched, as the initial allocation meant more Pakistani and Bangladeshi target populations resided in areas allocated to the control than intervention. The managers of HoB and BEN PCTs preferred that the outreach workers were given the opportunity to reach more people, thus, the randomisation was switched in consultation with the trial statistician and Independent Project Steering Committee.

Initially, we aimed to follow-up LSSS service users who achieved 4-weeks prolonged abstinence from smoking at three months from the agreed quit date. The Birmingham 'Call 2 Quit' line was unable to do this at three months. However six-month follow-up proceeded as planned.

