### Randomisation

We will use census super output areas (SOAs) as the unit of allocation[30]. In order to define these communities, initially all those SOAs within the study area with a combined Bangladeshi and Pakistani population of more than 10% will be identified and then mapped at ward level, enabling the street boundaries of each SOA to be seen. Contiguous SOAs will then be aggregated into natural communities (i.e. areas where people live, work, shop etc) using the local knowledge of the LSSS managers and advisors. SOAs in which more than 30% of the population are Pakistani and Bangladeshi will be considered to be high-density areas, while SOAs with 10–29% of the population being from these groups will be defined as low-density areas.

A total of 16 aggregated areas, sufficiently geographically dispersed, will be created to be randomised; there will thus be eight SOAs in each arm. For the randomisation, we will stratify, firstly by the proportion of Pakistani and Bangladeshi residents and secondly by absolute population size, to create eight areas that include high target population density and eight that are low-density areas. The high density areas will be further subdivided into those areas with target populations of Bangladeshi and Pakistani men above and below 10,000. The low density areas will be further subdivided into those areas with target populations above and below 300. Table 1 shows how the areas will be allocated. Randomisation will be undertaken by the study statistician who has no knowledge of the geographical areas using permuted blocks. Within each of the four strata, two areas will be randomly allocated to 'control' and two to 'intervention' arms. Maps of the final areas and their allocation to the two study arms are shown in Figures 1 and 2.

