**Figure 2 F2:**
[figure not shown]
**Map of randomisation areas in BEN PCT**.

**Table 1 T1:** Randomisation allocation

Number of areas	Bangladeshi and Pakistani population density	Bangladeshi and Pakistani population size	Study arm
2	High*	<10,000	Clinic only

2	High	<10,000	Clinic + outreach

2	High	>10,000	Clinic only

2	High	>10,000	Clinic + outreach

2	Low**	<300	Clinic only

2	Low	<300	Clinic + outreach

2	Low	>300	Clinic only

2	Low	>300	Clinic + outreach

*Pakistani and Bangladeshi populations = >30%

** Pakistani and Bangladeshi populations = 10–29%

In studies in which the number of units randomised is relatively small, stratified randomisation of communities should ensure equal distribution of key potential confounders. However, potential confounders are also important contextual factors affecting the success or otherwise of the interventions and thus possible effect-modifiers. We will therefore gather data on relevant aspects of the communities (in particular socio-economic position, since this is a strong predictor of smoking status) participating in the trial. Such data will be critical in enabling generalisation of the lessons learnt from this pilot trial.

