#### Denominator for the proportion of smokers setting quit dates

Our overall aim is to develop and refine the intervention, to pilot it, and have the data needed to inform sample size calculations for a definitive trial evaluating these interventions. In order to perform sample size calculations for a future trial, we aim to assess the reach of the interventions in attracting smokers wanting to quit. For the purposes of this study, reach has been defined as the proportion of each relevant ethnic group setting a quit date using the stop smoking service, with the denominator for this being all those of relevant ethnic group attempting to quit during the same period. We are estimating this latter number as it cannot be directly measured. We have searched a variety of sources to give information on the proportion of each ethnic group that attempted to quit in the past year and these data are not available. No local survey can truly randomly survey Pakistani and Bangladeshi populations because there is no publicly available local sampling frame that records ethnicity. Consequently, we will use the Smoking Toolkit Study to provide relevant data on the proportion of people that attempted to quit in the past year for the general population and assume that this figure is approximately the same in Pakistani or Bangladeshi men[34].

Stop smoking services routinely record information about each of their patients, including their age, gender, ethnic group, type of service used, medication used and outcome. This will be used to give both a before and after measure of the use of the service by the relevant groups (i.e. males of Pakistani and Bangladeshi ethnic group). Thus, we will have, for each area, the rate of use of the service for 12 months prior to the intervention that will serve as a baseline variable in the analysis (see Table 3). The after measure will be the same data collected for the 12 months during which the outreach workers are active. These data will be supplied anonymously from BEN and HoBt PCTs and this does not rely on data collection developed for the study. As noted above, the before-after design will allow control for intrinsic variability between areas. As such there will be no attempt to assess baseline balance between the intervention and control areas.

**Table 3 T3:** Use of LSSS by randomisation area residents for the baseline period (1st November 2006 – 31^st ^October 2007)

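### Arm labels were exchanged after allocation because of target population size, yet the plan declines a balance check, omits the size and density strata, and draws no consequence

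*Protocol article*

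**What the plan says.** The Randomisation section describes a concealed, stratified allocation: "Randomisation will be undertaken by the study statistician who has no knowledge of the geographical areas using permuted blocks". The four strata are defined by the density of the target population and then by its absolute size, and each stratum is divided evenly: "Within each of the four strata, two areas will be randomly allocated to 'control' and two to 'intervention' arms". The paragraph after Table 1 expects stratified randomisation to spread the main confounders evenly. It also undertakes to collect community data: "We will therefore gather data on relevant aspects of the communities (in particular socio-economic position, since this is a strong predictor of smoking status"). The stated use of those data is generalisation.

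Protocol amendments then reports what was done before the study began: "the randomisation of the intervention and control areas were switched, as the initial allocation meant more Pakistani and Bangladeshi target populations resided". The comparison meant is with the intervention areas: the control side had the larger number. On the motive, the same section says that the trust managers "preferred that the outreach workers were given the opportunity to reach more people, thus, the randomisation was switched". It adds that both the statistician and the steering committee were consulted. No change to the analysis or its interpretation is mentioned.

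The section on the denominator for quit dates argues that the before-after design controls for differences between areas, and concludes: "As such there will be no attempt to assess baseline balance between the intervention and control areas". The model given there is a multilevel Poisson regression. It has arm and the log prior-year count as covariates, the log of the estimated number wishing to quit as an offset, and a random area effect. That section also says the stratification will not be used in the analysis.

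**The concern.** Stratified randomisation by someone blind to the areas protects against confounding because nothing about the areas can influence the label. Here the label was settled after the allocation was known, and by an attribute of the areas. The arm that received outreach is the arm with more of the target population, by construction. Anything that goes with population size and also drives change in service use is then tied to arm in a consistent direction. It no longer averages out over possible allocations.

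The rest of the plan does not react. It keeps the expectation of balance, declines to look at balance, and excludes from the model the strata built on size and density, which include the attribute that triggered the switch. At stake is whether the uptake comparison, a primary study question meant to inform a definitive trial, can be read as an effect of outreach alone.

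**Working it through.** **1. The stated layout.** Table 1 has 8 rows of 2 areas: 8 × 2 = 16 areas, 8 per arm, matching the Randomisation section. Each stratum has 4 areas, split 2 and 2.

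**2. What the switch does to the allocation.** Possible allocations: C(4,2)^4 = 6^4 = 1,296. They form mirror pairs, each being one split with its labels reversed. A rule that outreach goes to the side with more of the target population keeps one of each pair: 1,296 / 2 = 648, barring ties. The split remains random and the label does not.

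**3. How uneven the areas are (Table 3).** Baseline users sum to 563. Areas 4 to 7 contribute 79 + 155 + 136 + 98 = 468, and 468 / 563 = 83%. The same four areas have 3 + 5 + 4 + 6 = 18 of the 23 pharmacies. Size of use and provider supply are therefore concentrated in the same places.

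**4. How far the rule can shift arm size.** The target populations are not tabulated, so Table 3 users stand in for them, and stratum membership is assumed. Enumerating all 1,296 allocations gives the intervention arm's share of baseline users:

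| Assumed strata | Random labels, mean | Larger side gets outreach, mean (range) |
|---|---|---|
| By rank of baseline use | 50% | 55% (51–63%) |
| Four largest areas spread over two strata | 50% | 63% (50–89%) |

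These figures describe arm size, not bias. The result depends heavily on the assumed strata.

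**5. Size per area, which matters more to a rate model.** With rank strata, the mean between-arm difference in log baseline users under the rule is 0.10. The SD across the 16 areas is 1.47, so the difference is 0.10 / 1.47 ≈ 0.07 SD. In some permitted allocations it is negative.

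**6. What the model covers, item by item.**
- Baseline level of use: covered by the log prior-year count, with a free coefficient.
- Size: partly covered. The count carries size, and the offset scales by the estimated number wishing to quit with a coefficient fixed at 1. Size not reflected in prior use is not freely adjusted.
- Density: not in the model. It defines the first level of stratification, which is left out.
- Provider supply: not in the model, although Table 3 lists pharmacies by area.
- Socio-economic position: to be collected, but given no role in the arm comparison.

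**7. What cannot be computed.** Table 3 has no arm or stratum column, and allocation appears only in Figures 1 and 2, which were not available to this review. The actual imbalance is unknown here.

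**The case against.** The strongest reply is that the planned analysis already deals with size. An offset model for rates does not need arms of equal total size. The prior-year count enters as a count, not a rate, with a free coefficient, so a log-linear trend in size as measured by prior use is already adjusted for. This stands, and it narrows the concern to what prior use does not capture.

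It is also true that the switch came before the study began, was disclosed with its reason, and involved the statistician and the steering committee. Table 3 gives use and pharmacies area by area, and Figures 1 and 2 are said to show the allocation. Comparison with outside areas, planned to detect contamination, would give some view of background change. These points lower the severity. They do not justify declining a balance table when the label was chosen by an area characteristic.

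Three stronger readings are tempting, and the documents do not support them:
- **That the trial is no longer randomised.** The partition of areas was still produced by permuted blocks; only the assignment of the label was decided.
- **That p-values are invalid because half the allocations could no longer occur.** Reversing all labels flips the sign of the arm contrast and keeps its absolute value, so a two-sided permutation p-value is the same on 1,296 or 648 allocations. No permutation test is planned in any case.
- **That a 55% share measures bias.** It measures arm size under assumed strata. If change in uptake is unrelated to the uncovered factors, there is no bias.

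**Conclusion.** The concern holds in a limited form. After a concealed stratified allocation was known, population size and managers' preference determined which set of areas received outreach. The plan gives this no consequence: it still expects balance, rules out assessing it and omits the strata. Trends in service use related to density, provider supply, socio-economic position, or size beyond what prior use reflects could enter the arm comparison.

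The size of any bias cannot be stated from the text. The shares of 55% and 63% rest on Table 3 users as a proxy and on assumed strata, and show only that arm sizes could differ appreciably. As this is a pilot and the switch preceded outcome data, the matter is one of reporting and sensitivity analysis; it does not invalidate the trial.

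**What to change.** 1. Delete the sentence that rules out a balance assessment. Tabulate by arm the target population, density, baseline uptake, number of pharmacies and socio-economic position.
2. Add one sensitivity analysis, stated before the arm comparison is examined, that adjusts for either the randomisation stratum (3 df) or log target population with a free coefficient (1 df). Do not use both: together they add 4 parameters on 16 areas, and they are likely to be collinear with each other and with the prior-year count. If the arm results have already been seen, since the article says analysis is under way, label it as post hoc.
3. State in the methods and in the conclusions that the arm labels were assigned by population size after randomisation, before the study began.

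No new data are needed beyond those held or already to be gathered. The cost is one table, one extra model that uses one to three degrees of freedom, and a more cautious conclusion.
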